|  | *Intervention*  *N=* | *Control*  *N=* | *Intervention*  *N=* | *Control*  *N=* |
| **Public, non-religious** | 9 | 5 | 16 | 1 |
| **Public, religious** | 20 | 14 | 24 | 41 |
| **Private** | 37 | 51 | 26 | 42 |

*In-school adolescent participants*

For both the intervention and control arms of the study, students will be invited to participate until 25 from each school assent (and whom have obtained parental consent). We will apply this predetermined cluster size to select the same number of students (n=25) per school in the intervention and control areas. Students in the control schools will be selected at random (from a list of all students between 10 and 14 years in the school), while those in the intervention area are self-selected based on their choice to participate in the intervention.

A total of 40 schools per study arm, equally distributed between Masina and Kimbanseke, will be selected. Altogether, 1,000 students will be enrolled in each school arm (intervention and control). Sample size calculation is detailed in the section, “Sample size and justification.”

*Parents of in-school adolescents*

All parents of in-school participants who consent their children to participate will be asked to participate in a baseline survey collecting sociodemographic information about themselves and household information.

*Out-of-school sample*

*Out-of-school adolescent participants*

Out-of-school participants will be recruited with the assistance of community-based organizations (CBOs) and religious organizations that work with OOSY in these communes. Specifically, KSPH will work with CBOs that serve out of school youth in each quartier and group (control or intervention) to create a list of eligible youth from which participants will be recruited. Youth whom have been out of school for 2 or more years will be prioritized due to the decreased likelihood that they will re-enroll in school during the study compared with youth who have been out of school for less time. A total of 400 out-of-school adolescents will be recruited in each arm of the GEAS cohort.

*Parents of out of-school adolescents*

All parents of out of-school participants will be asked to participate in a baseline survey collecting sociodemographic information about themselves and household information.

*Inclusion and exclusion criteria*

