**Sample size and justification**

In each arm of the study 1,400 youth will be recruited for a total of 2,800 participants. The intervention arm will include 1,000 ISY and 400 OOSY, and the control arm will also include 1,000 ISY and 400 OOSY.

The sample size calculation is based on the frequency of intervention endpoints, the effect size of the intervention, the cluster design and related design effect, as well as expected cohort attrition rate all calculated in the school sample.

We assume a cluster size of 25, an intra-class correlation of 0.15 and 20% attrition per cluster.

The power calculation for contraception is calculated among the girl sample (cluster of 10 girls per school accounting for the 20% attrition). Baseline contraceptive prevalence in Kinshasa among 15-17 year old adolescents is 13%, based on recent PMA2020 data collected in 2016. A cluster sample of 500 adolescents per group (40 clusters) will detect a doubling of contraceptive prevalence in the intervention arm with a power of 79%. The pregnancy rate of 5% based on PMA2020 estimate is too low to be able to detect a difference between intervention and control groups in this study.

Calculations were done using the Stata clustersampsi command for the two primary outcomes:

- Contraception: clustersampsi, binomial samplesize p1(0.13) p2(0.26) k(80) rho(0.2) alpha(0.05) beta(0.8)
- GBV: clustersampsi, binomial samplesize p1(0.10) p2(0.05) k(40) rho(0.02) alpha(0.05) beta(0.8)

All other indicators including attitudinal and knowledge measures are based on continuous scores. Calculations based on preliminary results from the gender norms scales from the pilot GEAS in Kinshasa indicate that a sample size of 800 adolescents (40 clusters of 20 adolescents each, after attrition) is sufficient to detect a 10% shift in the gender scores between the intervention and control groups.

Table 3. Sample size calculation

| **Endpoints** | *Control* | ***Effect size*** | *Intra-class correlation* | ***Power*** | ***N clusters /arm*** | ***Minimum average students/ cluster*** | ***N participants / arm*** |
| --- | --- | --- | --- | --- | --- | --- | --- |
| **Attitudes** |  |  |  |  |  |  |  |
| Stereotypical gender norms (continuous score 13 to 62) | *Scale 1 Mean=3.99*  *SD=0.59*  *Scale 2*  *Mean=3.55*  *SD=0.69* | *Scale 1 detectable different =0.14*  *Scale 2 detectable different =0.17* | *0.15* | *80%* | *40* | *20* | *800* |

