| Discussed contraception | *6%* | *RR=2.5* | *0.20* | *76%* | *40* | *20* | *800* |
| **Behavioral** |  |  |  |  |  |  |  |
| Proportion using modern contraception | *13%* | *RR=2* | *0.2* | *79%* | *40* | *11* | *440 girls* |
| Pregnancy | *5%* | *RR=0.5* |  | *27%* | *40* | *20* |  |
| Exposure to gender based violence in the last 6 Months (dichotomous) | *10%* | *RR=0.5* | *0.2* | *0.98* | *40* | *20* | *560* |

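### Table 3's GBV row is irreconcilable with itself and with the sample-size text: power for halving GBV is about 90%, 49% or 41% depending on which printed ICC is meant, and the stated 98% follows from none of them

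*Protocol*

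**What the plan says.** GBV exposure is one of the two primary outcomes in section I (Aims of the Study). The section on sample size and justification describes its calculation in three places.

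- The general assumptions: "We assume a cluster size of 25, an intra-class correlation of 0.15 and 20% attrition per cluster".
- The printed Stata command: "GBV: clustersampsi, binomial samplesize p1(0.10) p2(0.05) k(40) rho(0.02) alpha(0.05) beta(0.8", that is, 10% against 5%, 40 clusters, an ICC of 0.02 and a target of 0.8.
- The last row of Table 3, which gives control rate, effect, ICC and power as "Exposure to gender based violence in the last 6 Months (dichotomous) | *10%* | *RR=0.5* | *0.2* | *0.98", followed by 40 clusters per arm, 20 students per cluster and an N per arm of 560.

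Section IV agrees on the number of clusters: "A total of 40 schools per study arm, equally distributed between Masina and Kimbanseke, will be selected". The text on the gender-norm scales gives the cluster size left after dropout: "40 clusters of 20 adolescents each, after attrition". The section also says that the calculations were all made in the school sample. The 400 out-of-school youth per arm are therefore outside them.

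**The concern.** The row does not multiply out: 40 schools of 20 students is 800, not 560. Its ICC is ten times the one in the command that is printed as its source, and its power of 0.98 is not the command's target of 0.8. A reader cannot tell which assumptions produced the stated power.

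The choice matters because the ICC dominates power when there are only 40 clusters per arm. Read against 98% power, a null GBV result would look like near-proof that exposure was not halved, with a false-negative risk of 2%. Under the ICCs that the protocol prints, that risk in the school sample is about 10% at best and about 59% at worst.

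**Working it through.** **Inputs.** p1 = 0.10 and p2 = 0.05 (command; Table 3 as 10% and RR 0.5). k = 40 schools per arm (section IV, Table 3). m = 20 students per school after attrition (text, Table 3), with 14 (560/40) and 25 (no attrition) also tried. ICC 0.02 (command), 0.15 (general text) or 0.2 (Table 3). Alpha is 0.05. The protocol does not say whether the test is one- or two-sided; two-sided is assumed.

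**Formulas.** Effective n per arm = km / [1 + (m − 1) × ICC]. Power = Φ{[|p1 − p2|√n − 1.96√(2p̄(1 − p̄))] / √[p1(1 − p1) + p2(1 − p2)]}. With p̄ = 0.075, the second term in the numerator is 0.7301 and the denominator is 0.3708.

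**Check against the plan's other rows.** The same formula gives:
- contraception at ICC 0.2: 79.5% with 10 girls per school, 80.6% with 11 (stated 79%);
- discussed contraception at ICC 0.2: 76.7% (stated 76%);
- pregnancy, whose row prints no ICC, at the general 0.15: 26.8% (stated 27%).

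So the method matches the protocol's own to within one or two points. Only the GBV row is far off.

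**The GBV row as printed (ICC 0.2, m = 20).** Design effect 1 + 19 × 0.2 = 4.8. Effective n = 800/4.8 = 166.7. Power = Φ[(0.6455 − 0.7301)/0.3708] = Φ(−0.228) = 41.0%, against 98% stated.

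**All three ICCs, 40 schools per arm.**

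| ICC | 14 per school | 20 per school | 25 per school | Unlimited students |
|---|---|---|---|---|
| 0.02 | 80.9% | 89.9% | 93.8% | above 99.9% |
| 0.15 | 45.6% | 49.0% | 50.8% | 59.2% |
| 0.2 | 38.7% | 41.0% | 42.1% | 47.5% |

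The last column uses the limiting effective n, k/ICC: 2,000, 266.7 and 200 per arm. No planned cluster size gives 98%. At ICC 0.02 it takes about 40 students per school. One-sided testing does not rescue the figure: 94.5% at ICC 0.02 and 53.5% at ICC 0.2, both with 20 per school.

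**Where 560 comes from.** Without clustering, 80% power needs n = (0.7301 + 0.8416 × 0.3708)² / 0.05² = 434.4, so 435 per arm. The students needed per school are m = n(1 − ICC) / (k − n × ICC).
- ICC 0.02: 435 × 0.98 / (40 − 8.7) = 13.6, rounded up to 14, and 40 × 14 = 560. This is the printed command's answer, with 81% power.
- ICC 0.15: n × ICC = 65.25, which exceeds 40, so there is no solution.
- ICC 0.2: n × ICC = 87, which exceeds 40, so there is no solution.

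**Schools needed per arm for 80% at 20 students each.** 435 × 4.8/20 = 104.4, about 105, at ICC 0.2. 435 × 3.85/20 = 83.7, about 84, at ICC 0.15. The 87 above is only the limit for unlimited students per school at ICC 0.2.

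**Detectable at 80% power with 40 × 20.** From 10% down to 5.6% (ICC 0.02), 3.2% (0.15) or 2.6% (0.2).

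**The case against.** The strongest reply is that 0.2 in the table is a decimal slip for 0.02. The GBV command prints 0.02, and 560 can be recovered only from that value. If so, the planned 40 × 20 gives 90% power, above the command's target. A reader of Table 3 might infer that the study has about 40% power for GBV and can never reach 80% with 40 schools per arm. The documents do not support that as a flat statement; it holds only if 0.2 is meant (or, with 49% power, 0.15). Equally, the slip is not proven. The other binary rows with a printed ICC use 0.2, and the protocol gives no reason for a GBV value one-tenth as large. Even if it is a slip, 98% remains wrong.

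A second reply is that 0.15 is a general statement that the table applies only to the attitude scales, so the direct conflict for GBV is 0.02 against 0.2. That is fair. The text does not limit 0.15 to those scales, however, so it still needs aligning.

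Third, a reader might infer that the trial as a whole would miss a true halving about six times in ten. That also goes too far. The calculation covers the school sample, and the 400 out-of-school youth per arm could add information. Assuming 20% attrition among them too (320 per arm) and pooling, power at ICC 0.2 would be 84% if they were unclustered, 68% at a design effect of 2 and 60% at 3. The protocol does not say that the samples are pooled for GBV, so these are illustrations only.

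Finally, several sets of inputs that the row does not state can be made to yield about 98%. None is documented, so the figure should not be attributed to any of them.

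**Conclusion.** The point stands as an irreconcilable power statement for a primary outcome. For a halving from 10% to 5% (two-sided 5%, school sample, 40 schools of 20 students per arm), power is about 90% if the ICC is 0.02, 49% if 0.15 and 41% if 0.2. The stated 98% follows from none of these at 14, 20 or 25 students per school. The stated 560 belongs to a different calculation (ICC 0.02, 14 per school, 81% power) from the ICC, cluster size and power printed beside it.

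Whether the school sample is adequately powered turns on an ICC that the protocol does not settle. At 0.02 it is. At 0.15 or 0.2, 40 schools per arm fall short at any cluster size, with ceilings of 59% and 47.5%. That 98% is wrong does not depend on which ICC is chosen, nor on the assumption of two-sided testing.

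**What to change.** Choose one ICC for GBV, give its justification, and use it in the text, the command and Table 3. In the GBV row, replace 560 with N = 800 (40 × 20) and 0.98 with the matching figure:

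| ICC chosen | Power, 10% against 5% | Detectable at 80% power |
|---|---|---|
| 0.02 | 90% | 10% to 5.6% |
| 0.15 | 49% | 10% to 3.2% |
| 0.2 | 41% | 10% to 2.6% |

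State that the test is two-sided (or give the figures for the test intended) and that the row applies to the school sample only.

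The restated row would still describe a halving, whereas section I sets the GBV outcome as a 10% decrease and the societal-benefits answer hypothesises 20%. The row should say plainly which effect it addresses.

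The cost is some wording and one table row, and a stated power that is less favourable than the present one. No participants are added.

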**V. Study Procedures**

The role of Hopkins researchers in the present application is primarily development, design, oversight and coordination of the research.

*Training of interviewers*

During Phase 1 a 1-day training-of-trainers session was held in June 2015 that included the site-PI ([name]) and field coordinator ([name]) that focused on the implementation of data collection platform using tablets equipped with ODK software. The KSPH team is well versed to mobile technology platform data collection, as they have pioneered this type of platform through the PMA2020 project in Kinshasa over the last 3 years. In addition, [name] and [name] have completed the CITI Hopkins training for human subjects research and have active certificates.

KSPH successfully adapted and used GEAS training materials provided by Hopkins to train 20 interviewers over 3 days for the pilot conducted in February 2016. With the help of the Hopkins team, KSPH will adapt the training material for Phase 2 of the GEAS. The 5-day training will include the following:

- Research instruments
- Adolescence from a developmental perspective
- Consent and assent process: principles and role playing
- Identifying, managing and reporting case of child abuse
- Confidentiality and privacy
- The art of interviewing
- Data collection and transmission using ODK software on tablets

1. Recruitment Process:

**In-school participants**

As described in Section IV, “Participants,” above, our intervention partners at Save the Children recently conducted a mapping exercise with guidance from KSPH researchers, the results of which have aided in our determination of recruitment sites.

Prior to study recruitment, the KSPH research team will inform the ministry of education, the ministry of health, and the national council for adolescent health “PNSA” (Plan National pour la Santé des Adolescents) about the schools and community organizations participating in the GEAS evaluation. The ministry of education will provide a signed letter for school directors acknowledging that the school has been selected to participate in the GEAS study.

- Control participants

Trained research interviewers hired by KSPH will visit each selected school in the control area to explain the research to them, and obtain their approval for their students to participate in the study. Working with the school directors, the KSPH team will establish a list of eligible students (10-14 years of age) attending the school in order to draw a random sample of 25 adolescents per school with replacement to participate in the longitudinal study. The school director will then organize a short meeting at the end of class with the eligible students to indicate that they have been selected for a study on gender and health in their community and that their parents will be informed about the study and invited for an information session at the school. The director will indicate to the students that their teachers will inform them about the time and place of data collection. Formal permission from school directors and community organizations (after-school programs, scout organizations, sports clubs for youth) will be obtained if data collection takes place in their facilities.

Next, the school-parent committee (PTSA) will send a letter to parents of selected students informing them that their child has been selected for participation in the study and indicating that interviewers from KSPH will be hosting an information session with a given date and time at the school. The parent information session will describe the study goals and procedures, and the risks and benefits of participating. In addition, they will be explicitly informed of their child’s confidentiality and the procedures in place in the event of disclosure of abuse. Parents will be asked at the end of the session if they consent for their child to participate and if they themselves consent to participate in the baseline questionnaire. If parents give consent to both, they will be asked to complete the short (15 minute) questionnaire, either by themselves (CASI) if they can read and navigate a tablet on their own, or with the help of an interviewer (CAPI).

After parents have provided consent for their children’s participation, adolescents will be informed and reminded by their teachers regarding the time and place of data collection and whether it will take place in the school facilities or in a communal area (church or community building) near the school, depending on the availability school facilities. All adolescents from the same school will be convened at the same time. Before data collection, the adolescents will be collectively informed about the study goals, procedures, and the consent procedure including the protocol for child abuse disclosure. At the end of the information session, children will have an individual conversation with his/her interviewer in order to assent to participate. After assent has been given, data collection will proceed.

- Intervention participants

Save the Children employs locally based intervention experts whom will take charge of recruitment of adolescents participating in the intervention by approaching schools within our target communes of Masina and Kimbanseke. Save the Children will establish a list of children participating in the intervention, and, of these, 25 will be randomly selected for participation in the study (if the intervention includes more than 25 students). Save the Children will facilitate the introduction of the KSPH team who will visit the school director of each selected school in the intervention arm to explain the GEAS research and obtain approval for their students to participate in the longitudinal study. School directors will provide the KSPH team with a list of all adolescents aged 10-14 years in the school in order to assess the potential selection bias of voluntary participation in the intervention (criteria for being in the intervention arm). Formal permission from school directors and community organizations (after-school programs, scout organizations, sports clubs for youth) will be obtained if data collection takes place in their facilities.

The process for recruitment of in-school intervention participants follows the same as that for in-school control participants, outlined above. Specifically, the school director will organize a short meeting at the end of class with the eligible students to indicate that they have been selected for a study on gender and health in their community and that their parents will be informed about the study and invited for an information session at the school. The director will indicate to the students that their teachers will inform them about the time and place of data collection.

Next, the school-parent committee (PTSA) will send a letter to parents of selected students informing that their child has been selected for participation in the study and indicating that interviewers from KSPH will be hosting an information session with a given date and time at the school. The parent information session will describe the study goals and procedures, and the risks and benefits of participating. In addition, they will be explicitly informed of their child’s confidentiality and the procedures in place in the event of disclosure of abuse. Parents will be asked at the end of the session if they consent for their child to participate and if they themselves consent to participate in the baseline questionnaire. If parents give consent to both, they will be asked to complete the short (15 minute) questionnaire, either by themselves (CASI) if they can read and navigate a tablet on their own, or with the help of an interviewer (CAPI).

After parents have provided consent for their children’s participation, adolescents will be informed and reminded by their teachers regarding the time and place of data collection and whether it will take place in the school facilities or in a communal area (church or community building) near the school, depending on the availability school facilities. All adolescents from the same school will be convened at the same time. Before data collection, the adolescents will be collectively informed about the study goals, procedures, and the consent procedure including the protocol for child abuse disclosure. At the end of the information session, children will have an individual conversation with his/her interviewer in order to assent to participate. After assent has been given, data collection will proceed.

**Out-of-school participants**

- Control participants

KSPH will call upon standing relationships with community relays whom assisted in recruitment of participants in Phase 1 of the GEAS, along with staff from CBOs assisting with the recruitment of OOSY for the intervention, to create a list of eligible OOSY from which KSPH will recruit participants. As previously noted, youth who have been out of school for 2 or more years will be prioritized, then separating girls and boys and then sampling by age 200 adolescents from Masina and 200 from Kimbanseke.

After the sampling, KSPH will work with alongside RECOPE (Reseau Comunitaire de Protection de l'Enfant, child protection organization) members, who will facilitate house calls for KSPH researchers to meet with the parents of eligible adolescents. At those meetings, parents will be informed of the study goals and procedures and the risks and benefits of participating. In addition, they will be explicitly informed of their child’s confidentiality and of the procedures in place in the event of disclosure of abuse. At the end of the meeting, parents will be asked if they consent for their child to participate and if they themselves consent to participate in the baseline questionnaire. If parents give consent to both, they will be asked to complete the short (15 minute) questionnaire, either by themselves (CASI) if they can read and navigate a tablet on their own, or with the help of an interviewer (CAPI).

After parents have provided consent for their children’s participation, an appointment will be made for the adolescents will be informed and reminded by RECOPE members and other engaged community leaders regarding the time and place of data collection and its location (in a communal area such as a church or community building), which will be near their homes. A group of adolescents from the quartier will be convened, and the adolescents will be collectively informed about the study goals, procedures, and the consent procedure including the protocol for child abuse disclosure. At the end of the information session, children will have an individual conversation with his/her interviewer in order to assent to participate. After assent has been given, data collection will proceed.

Participants will be given as much privacy as possible, and data collection will occur in unobtrusive times/settings (i.e. participants will not miss class or be singled out), but it cannot be guaranteed that their involvement in the study will be private. Adolescent participants and their parents will be made aware of this fact at the time of consent/assent, as well as of the fact that they are free to leave the study at any time without penalty.

- Intervention participants

Save the Children will work with CBOs that serve OOSY in each quartier or section of the commune to recruit youth for involvement in the intervention and will create a list of eligible OOSY from which KSPH will recruit participants. As previously noted, youth who have been out of school for 2 or more years will be prioritized. These organizations will facilitate the distribution of letters informing parents of eligible adolescents about the study goals. RECOPE members will facilitate meetings between parents of eligible youth and researchers from KSPH. At those meetings, parents will be informed of the study goals and procedures and the risks and benefits of participating. In addition, they will be explicitly informed of their child’s confidentiality and the procedures in place in the event of disclosure of abuse. Parents will be asked at the end of the session if they consent for their child to participate and if they themselves consent to participate in the baseline questionnaire. If parents give consent to both, they will be asked to complete the short (15 minute) questionnaire, either by themselves (CASI) if they can read and navigate a tablet on their own, or with the help of an interviewer (CAPI).

After parents have provided consent for their children’s participation, adolescents will be informed and reminded by RECOPE members and other engaged community leaders regarding the time and place of data collection and its location (in a communal area such as a church or community building), which will be near their homes. A group of adolescents from the quartier will be convened, and the adolescents will be collectively informed about the study goals, procedures, and the consent procedure including the protocol for child abuse disclosure. At the end of the information session, children will have an individual conversation with his/her interviewer in order to assent to participate. After assent has been given, data collection will proceed.

Intervention activities will be available and open to youth enrolled in the study and also whom are not. That is, participants enrolled in the intervention group will be encouraged to participate, but they will do so alongside peers who may not be enrolled for any reason.

Regarding participation in the survey itself, participants will be given as much privacy as possible, and data collection will occur in unobtrusive times/settings (i.e. participants will not miss class or be singled out), but it cannot be guaranteed that their involvement in the study will be private. Adolescent participants and their parents will be made aware of this fact at the time of consent/assent, as well as of the fact that they are free to leave the study at any time without penalty.

1. Consent Process:

After parents have been notified of the study as described in Section A above, KSPH researchers will be responsible for obtaining parental consent and youth assent. These researchers are trained in research ethics and best practices, and will have been CITI certified in advance of recruitment, consent, and baseline data collection.

With the assistance of school directors and PTSAs, KSPH researchers will organize informational meetings for parents of eligible ISY at which consent for participation will be sought. With the assistance of youth-serving CBOs familiar with community members and other community representatives, KSPH data collectors will visit the homes of OOSY to inform parents of eligible adolescents about the study goals, procedures, risks and benefits and the opportunity to participate. Both parents and adolescents will be aware before the time of consent of whether the adolescent participant would be in the intervention or control arm of the study.

The researcher will obtain written informed consent from the parent for the adolescent’s participation and their own participation; or, in the event that they are unable to sign, they may make their mark. The parent will be provided a copy of the informed consent form to keep with contact information of the study staff for reference. The researcher or community liaison will serve as a witness to the consent process and will counter-sign the forms to indicate that they properly obtained consent from the parent. The same process will be conducted to obtain assent from the adolescent prior to baseline data collection.

Given the longitudinal nature of the study and the fact that it is confidential but not anonymous, special procedures will be undertaken so as to assure that data are secure and that participants can be assured of absolute confidentiality (see Section VI below for procedures). Additionally, since sensitive data will be collected including data indicating potential exposure to gender-based violence and abuse, participants will be advised in advance that reporting of certain events may result in a report to authorized child protection services.

Thus, during the consent process we will be explicit with both potential participants and their parents about what kind of information will be collected. Specifically, participants will be assured that information will be confidential and will not be shared except in cases of exposure to sexual or physical abuse that requires notification to authorities. In such cases data collection will cease immediately, and, with the permission of the adolescent participant (when the event involves those other than parents and immediate family), parents will be informed and the data collector will notify his or her filed coordinator who in turn notifies the site-PI ([name]), who will then prepare the report to the appropriate organization and/or agency. At that point the Hopkins study PI ([name]) will also be notified and in turn he will notify the JHBSPH IRB in accordance with JHU guidelines. When the events involve a parent or close family member, notification will go to a pre-selected organization tasked with protection of children and minors, who will pursue the investigation and the remainder of the reporting process will remain unchanged.

